#### Exploratory endpoints

For exploratory scientific analyses, biomaterial (serum, plasma, urine, waste plasma from TPE) will be acquired longitudinally (at randomization, 12 and 24 h, as well as 3, 7, and 14 days following randomization) and multiple predefined scientific subprojects are planned.

### Participant timeline

A time schedule of enrolment, interventions, assessments, and visits for participants (SPIRIT Figure) is given as a schematic table (Table 2).

**Table 2 Tab2:**
[figure not shown]
Schedule of Enrollment, Interventions and Assessments (SPIRIT Figure)

### Sample size

The primary aim of the study is to demonstrate superiority of SOC + TPE compared to SOC alone with regard to the primary endpoint 28-day mortality. In a prospective, monocentric, non-controlled pilot study of the TPE treatment in patients with septic shock, the observed 28-day mortality rate was 65%, while the predicted mortality rate using the APACHE-II-score was as high as 91% [10]. Meanwhile, two randomized clinical trials have been conducted. In one (small, *n* = 20 vs 20) randomized control trial, the observed mortality rate of the TPE-treated patients was 40% in contrast to 50% in the control group, resulting in a risk difference of − 10% with a 95% CI of [− 0,41;0,21] [14]. In another randomized control trial, the observed mortality rate of the treated patients was 33.3 and 53.8% in the control group, resulting in a risk difference of − 21% with a 95% CI of [− 0.39; − 0.02] [8]. For sample size calculation, we considered the two RCTs only and combined the outcome in a meta-analysis. The treatment procedures were similar, and the two trials are very homogeneous (I2 of 0%). The meta-analysis resulted in a risk difference of − 18% with a 95% CI of [− 0.34; − 0.02]. This risk difference was used in the sample size calculation. Sample size calculation was done for a two-group continuity corrected chi-square test (Query Advisor 8.7.1.0). To detect a reduction in 28-day mortality rate from 60 to 42% in the experimental group with a two-sided type I error rate of 5% and a power of 80%, at least 131 patients per group are required. Thus, the total sample size to detect the expected effect on the 28-day mortality is 262 patients. Stratification for sex, center, pulmonary focus of infection (yes/no), and lactate (< / ≥ 4.5 mmol/) at randomization is assumed to increase power of the statistical test. Considering a drop-out rate of 5%, a total of 274 patients will be assigned to the trial, i.e., recruited.

### Recruitment

The EXCHANGE-2 study group will secure adequate recruitment and conduction of the trial. Every week during the trial period, the recruitment numbers will be assessed, monitored by the Hannover Clinical Trails Center (Zentrum für Klinische Studien (ZKS)) and will be reported to the principal investigator. Patients under investigation are critically ill and therefore drop-out or loss to follow-up or other intercurrent events are unlikely to hinder the observation of the primary endpoint.

### Assignment of interventions: allocation

Permuted block randomization with variable block length stratified by sex, center, pulmonary focus of infection (yes/no), and lactate (< / ≥ 4.5 mmol/) at randomization will be used to allocate patients to both study arms. Only the statistician and the unblinded data manager will have access to the randomization list. The allocation is performed via the eCRF system. Only after the patient has been documented with in- and exclusion criteria in the eCRF by the study site, the allocation of the patient to a treatment group will be displayed in the eCRF automatically according to the sequence determined by the randomization list. For the study sites, it is not possible to see the randomization list.

### Blinding

The clinical team responsible for the participant (physicians, nurses, and others) involved with direct patient care will not be blinded to allocation group due to the inherent difficulty in blinding the intervention. Measures will be taken to ensure that the information about allocation will not disseminate beyond the immediate group of caregivers responsible for patient care. The intensive care physician will not be allowed to share any information regarding the allocation group. Patients, their legal representatives, and family will only be informed that the patient has been randomized into the study. Health personnel responsible for outcome assessment at follow-up will be blinded to the allocation of the intervention when possible.

The author group, trial statistician, and the trial coordinating team will be blinded to group allocation. In order to enable an unbiased assessment of the intervention and manuscript writing process, the two study arms will be coded as “X” and “Y”. Two manuscripts will be drafted one assuming that “X” corresponds to the TPE group and “Y” to the control group—and one draft assuming the contrary. The code will be broken upon acceptance of both drafts by the author group.

### Data collection and management

#### Data management

All study data will be collected by the investigator and/or other study personnel. An online clinical trial data base is provided, in which the data are entered via an electronic Case Report File (eCRF). Authorized and trained staff of the study sites will enter the data in the eCRF. SAEs will additionally be documented on paper forms. Verification of the data in the eCRF occurs by monitoring as well as via range, validity, and consistency checks programmed in the system. Additionally, manual queries can be raised in the system by authorized study staff if further discrepancies are detected. Based on the queries, the investigator can review and answer the found discrepancies directly in the system. All changes of data entered in the eCRF can be followed by an audit trail. A quality control will be performed before the database is closed. This procedure is documented. Finally, data transfer takes place for statistical evaluation.

#### Data protection

All study staff has to give due consideration to data protection and medical confidentiality. The collection, transfer, storage, and analysis of personal study-related data are performed pseudonymized according to national regulations. This trial will conform in its entirety with the Regulation (EU) 2016/679 of the European Parliament and of the Council of 27 April 2016 on the protection of natural persons with regard to the processing of personal data and on the free movement of such data. The declaration of data protection is contained within the patient information/informed consent form.

#### Data safety and monitoring board

An independent Data Safety Monitoring Board (DSMB) will be implemented to detect possible harms and to assure continuous risk/benefit assessment. The DSMB is a group of independent experts external to the clinical investigation assessing the progress, safety data, and if needed, critical efficacy endpoints. The members of the DSMB are the following: [name]. [name], UK Jena, Zentrum für klinische Studien & Center for Sepsis Care and Control; [name]. [name], UK Bonn, Institut für Experimentelle Hämatologie und Transfusionsmedizin; [name]. [name], Apherese Forschungsinstitut, Köln, Universitätsmedizin Mainz; [name] [name], UK Jena, Institut für Biometrie, Co-Speaker of the Center for Sepsis Control and Care (CSCC).

### Collection and storage of biomaterial 

Blood samples of approx. < 40 ml (2 × serum, 2 × plasma, 2 × citrate, 2 × hirudin S-Monovette for immunostimulation assay, and 1 × Streck – Cyto-Chex BCT tube for immunophenotyping) and urine samples of approx. 15 ml (2 × urine) will be obtained at Visit 2 (at randomization, BIO-1), at visit 4 (12 h after randomization, BIO-2), at visit 5 (24 h after randomization, BIO-3), at visit 6 (48 h after randomization, BIO-4), at visit 10 (day 7, BIO-5), and visit 11 (day 14, BIO-6) for the evaluation of the planned exploratory endpoints. Additionally, 20 ml of the removed plasma will be collected (in the treatment group only) at visit 3 (TPE-1) and (if a second TPE is performed) at visit 5 (TPE-2). Details regarding the collection, processing, storage, and shipment of samples will be included in the lab manual.

### Statistical methods

#### Analyses populations

The intention-to-treat (ITT) population comprises all randomized patients. Patients will be analyzed as randomized independently of the performed intervention. Primary analyses of all efficacy endpoints will be conducted on the ITT population.

The per-protocol (PP) population comprises all patients that received the randomized intervention and were complying with the study protocol until the end of the follow-up period. Supplementary efficacy analyses will be conducted on the PP population.

The safety population comprises all patients that received the study intervention. Patients will be analyzed as treated. Analyses of safety endpoints will be conducted on the safety population.

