### Trial design

This is a randomized, prospective, multicenter, open-label, controlled, parallel-group interventional trial to test superiority of adjunctive TPE over standard of care treatment in patients with early septic shock. The study will have two arms: a treatment arm, in which patients receive a singular session of TPE using fresh frozen plasma (FFP) as replacement fluid (optional second TPE session after 24 h possible, see below) and a control arm, in which patients are treated with the current SOC (Fig. 1). The primary endpoint is 28 days mortality. Study participants will be followed up at 90 days and 1 year following study inclusion. This study is an investigator-initiated trial funded by the German Research Foundation (DFG, DA 1209/7–1).

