The patient information/informed consent form and the consent form for acquiring biomaterial have to be signed in duplicate by the patient/legal representative and the investigator. One document will be given to the patient/legal representative, the other one remains in the trial investigator file (TIF) at the trial site. No study procedures are allowed to be conducted until patient’s/legal representative written informed consent has been obtained. The patient information/informed consent form has to be revised whenever important new information becomes available that may be relevant to the subject’s consent. The patients have to be informed and asked to give their consent to continue study participation by signing the updated form. Participation in this clinical trial is voluntary. Withdrawal from the trial at any time and for any reason is without any disadvantages to the patient’s further treatment. In order to enable an unbiased assessment of the primary endpoint, and given that informed consent from the patient/ legal representative is required in order for the patient to be included into the trial, the endpoint of mortality at 28 days will be obtained from all patients and analyzed in the form of an intention-to-treat analysis, indiscriminate of a withdrawal of consent at a later point. In case of a patient’s withdrawal of informed consent, all study data collected up to the point of consent withdrawal will be anonymized and employed for further analyses solely in its anonymized form. However, in cases for which data from formally withdrawn patients is of relevance for the security assessment of this trial, anonymization will be delayed and only performed at an unspecified later point in time when security clearance is given by the trial responsible.

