#### Analysis of the primary endpoint

The primary endpoint 28-day mortality (dead at 28 days: yes or no) which will be analyzed using a logistic regression model adjusting the treatment effect for sex, pulmonary focus of infection (yes/no), baseline lactate (< 4.5/ ≥ 4.5 mmol/l), and center will be used. Superiority of the experimental intervention compared to the control intervention can be concluded if the upper boundary of the two-sided 95% confidence interval for the adjusted odds ratio (experimental intervention / control intervention) is below 1.

Patients will be followed up even after premature discontinuation of study intervention, and all collected data will be used in the primary analysis. Since patients enrolled in this study are critically ill, the rate of drop-out and loss to follow-up is expected to be very low. Nevertheless, if the vital status at day 28 is unknown for a patient, this patient will be considered dead at day 28 in the primary analysis.

As a sensitivity analysis, the missing vital status at day 28 will be handled using the multiple imputation.

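### The per-protocol set requires compliance to the end of follow-up (1 year on the plain reading), so breaches after day 28 could remove survivors, and only survivors, from a 28-day mortality analysis

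*Protocol article*

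**What the plan says.** Under Analyses populations, the protocol article defines the PP population as "all patients that received the randomized intervention and were complying with the study protocol until the end of the follow-up period". Its use is stated in one line: "Supplementary efficacy analyses will be conducted on the PP population". No endpoint is named or left out, and no time limit is set per endpoint.

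That section does not put a number on the follow-up period. Trial design does: "Study participants will be followed up at 90 days and 1 year following study inclusion". Table 1 lists 1-year mortality as a secondary endpoint. On the plain reading, follow-up therefore ends at 1 year.

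The main efficacy endpoints close much earlier: 28-day mortality and organ support-free days at day 28, and mean SOFA at day 7.

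The PP set is not the main analysis set: "Primary analyses of all efficacy endpoints will be conducted on the ITT population". For the primary endpoint, the consent section adds that "the endpoint of mortality at 28 days will be obtained from all patients and analyzed in the form of an intention-to-treat analysis", whether or not consent is withdrawn later.

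**The concern.** A patient who has died by day 28 cannot afterwards withdraw or breach the protocol. A patient alive at day 28 can. If PP membership is judged over a full year, whether a patient counts in a 28-day analysis may depend on something that happens after the endpoint is settled and that only one outcome group can do. That is selection on the outcome. It is separate from the usual PP question of who received plasma exchange.

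At stake is the one supplementary efficacy analysis that the article restricts to adherent patients. Late exclusions would raise its mortality rates. If they were uneven between arms, its odds ratio would move for reasons unrelated to 28-day mortality. The same logic applies to mean SOFA (events after day 7) and organ support-free days (events after day 28), where deaths also receive the worst values.

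**Working it through.** **Reading the definition.** Three readings are possible.

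1. Compliance until death or 1 year, whichever comes first. This is the usual sense, and survivor-only exclusion follows from it.
2. Compliance literally through 1 year, so that a patient who dies earlier does not qualify. Every 28-day death would then leave the set and PP mortality would be 0% in both arms. This cannot be intended.
3. Compliance to day 28. This causes no problem, but the text does not say it.

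The rest uses reading 1.

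**Inputs from the document.** Sample size section: a "reduction in 28-day mortality rate from 60 to 42% in the experimental group", two-sided 5% error, 80% power, continuity-corrected chi-square test, 131 per group. Abstract: 137 per arm recruited.

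**The plan's own figure.** With mean rate 0.51 and difference 0.18:
- uncorrected n = [1.960 × √(2 × 0.51 × 0.49) + 0.842 × √(0.60 × 0.40 + 0.42 × 0.58)]² / 0.18² = 119.9, rounded up to 120
- corrected n = (119.9 / 4) × [1 + √(1 + 4 / (119.9 × 0.18))]² = 130.8, rounded up to 131

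The stated 131 per group is reproduced, so 60% and 42% are a sound base.

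**Assumption, not in the document.** A share x of day-28 survivors is excluded for a later breach, with x from 5% to 20%.

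**Formulas.** With p the 28-day mortality in an arm:
- PP mortality = p / [p + (1 − p)(1 − x)]
- PP odds ratio = true odds ratio × (1 − x in control) / (1 − x in TPE)

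True odds ratio = (0.42/0.58) / (0.60/0.40) = 0.483.

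Worked case, 5% in both arms: control 0.60 / (0.60 + 0.40 × 0.95) = 0.60 / 0.98 = 61.2%; TPE 0.42 / (0.42 + 0.58 × 0.95) = 0.42 / 0.971 = 43.3%.

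| Excluded survivors, control / TPE | PP mortality, control | PP mortality, TPE | Difference (points) | Odds ratio |
|---|---|---|---|---|
| none | 60.0% | 42.0% | −18.0 | 0.483 |
| 5% / 5% | 61.2% | 43.3% | −18.0 | 0.483 |
| 10% / 10% | 62.5% | 44.6% | −17.9 | 0.483 |
| 20% / 20% | 65.2% | 47.5% | −17.7 | 0.483 |
| 10% / 5% | 62.5% | 43.3% | −19.2 | 0.457 |
| 5% / 10% | 61.2% | 44.6% | −16.6 | 0.510 |
| 20% / 10% | 65.2% | 44.6% | −20.6 | 0.429 |
| 10% / 20% | 62.5% | 47.5% | −15.0 | 0.543 |

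Differences are taken before rounding.

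**No true effect.** The odds ratio equals the ratio of retained shares at any baseline mortality: 0.8/0.9 = 0.889 for 20% / 10%, and 0.9/0.8 = 1.125 for 10% / 20%.

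**Headcount.** With 137 per arm, expected day-28 survivors are 137 × 0.40 = 54.8 (control) and 137 × 0.58 = 79.5 (TPE). A 5% share is about 3 and 4 patients, 10% about 5 and 8, and 20% about 11 and 16.

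**The case against.** The case for leaving the text alone has four parts.

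- **The rule is partly inferred.** The PP paragraph gives no length for follow-up, does not name 28-day mortality, and does not say that withdrawal or a missed 90-day or 1-year contact is non-compliance. Which deviations exclude a patient is commonly settled in the full protocol or analysis plan, which are not shown. This stands as a limit: the effect is conditional on late breaches counting. It does not remove the point, because the article does fix the time window, and that window is too long for the 28-day and 7-day endpoints.
- **Uneven loss is less likely than an open-label design suggests.** A reader might infer that unblinded patients would withdraw differently by arm. The Blinding section works against that: patients, representatives and family are told only that randomization took place, and follow-up assessors are blinded where possible. This lowers the risk. It does not exclude it, because survivors may differ in health between arms if treatment changes who survives.
- **Loss is expected to be low.** The article plans for 5% drop-out and expects very little loss. Those statements are made in connection with the primary endpoint, so they do not settle compliance to 1 year. They are still a reason to give weight to the 5% rows.
- **No decision rests on the PP set.** This stands in full. The primary test uses ITT, and the key secondary tests follow in order from the primary result.

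**Conclusion.** The PP definition is badly fixed for endpoints that close before 1 year. If breaches after day 28 count, they can remove only day-28 survivors, and PP 28-day mortality rises in each arm where that occurs: by 1.2 to 1.3 points at 5% late exclusion, and by 5.2 to 5.5 points at 20%.

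Two stronger conclusions are tempting and not supported. One is that the PP analysis necessarily overstates mortality in both arms; an arm with no late exclusions is unaffected. The other is that the odds ratio is biased as the plan stands; equal exclusion leaves it at 0.483. It moves only with unequal exclusion (0.457 or 0.510 for 5% and 10%; 0.429 or 0.543 for 10% and 20%), and the document gives no basis for predicting the direction.

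The result rests on follow-up ending at 1 year, on late breaches counting as non-compliance, and on assumed exclusion rates. The ITT result, the key secondary sequence and the sample size are untouched. It is a modest defect in a supplementary analysis, worth correcting before data are seen.

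**What to change.** In the PP definition, replace the reference to the end of follow-up with compliance from randomization up to the time point of the endpoint being analysed or death, whichever comes first: day 28 for 28-day mortality and organ support-free days, day 7 for mean SOFA, and the corresponding time point for later endpoints. State that withdrawal or any other breach after that point does not remove a patient from that endpoint's analysis.

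On the planning rates, no day-28 survivor is then lost for a later event, and the figures stay at 60% vs 42% with odds ratio 0.483. Breaches inside the window can still be related to outcome, as in any PP analysis; the change removes only the part caused by later events.

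The cost is one changed sentence and no new data. The PP set will differ by endpoint, so its size must be reported for each, and it may become slightly larger.

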#### Study procedure (treatment arm): therapeutic plasma exchange (TPE)

The TPE treatment will be initiated within 6 h after randomization. Duration of TPE treatment is approximately 120–180 min. An additional second TPE can be performed at 24 h following randomization if the patient has responded to first treatment as indicated by any reduction of NE dose *and* if NE dose is still ≥ 0.4 µg/kg/min after 24 h. Both unfractionated heparin (UFH) and citrate may be used as anticoagulant medication. To ensure treatment comparability between different patients, we will replace plasma in a fixed ratio of 1.2 × the individual patient’s total plasma fluid. The individual patient’s total plasma fluid will be calculated on each trial site from hematocrit and body weight (BW) following the formula by Kaplan et al. (16). The formula used calculates the estimated plasma volume (ePV) as: *ePV* = *[[0.065* × *BW* [kg]*)]* × *[100-Hematocrit* [%]*]]* × *10* [ml]. To avoid potential allergic reactions, anti-histamines (Clemastin (Tavegil®) 2 mg and Ranitidin (Ranitic®) 50 mg, both given as intra-venous (i.v.) push), will be administered before TPE (and in the control group at time of randomization). No additional cortisone push should be given as anti-allergic prophylaxis immediately before TPE treatment.

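### The per-protocol definition drops TPE-arm patients who die before TPE but, on its natural reading, keeps SOC patients who die in the same hours; this component tilts the supplementary analyses toward TPE

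*Protocol article*

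**What the plan says.** Under Analyses populations, the protocol article sets two conditions for the PP set. The first is receipt of treatment: "The per-protocol (PP) population comprises all patients that received the randomized intervention". The second is that these patients "were complying with the study protocol until the end of the follow-up period". The set has a limited role: "Supplementary efficacy analyses will be conducted on the PP population". The main results come from the set of all randomized patients: "Primary analyses of all efficacy endpoints will be conducted on the ITT population".

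The section on the treatment arm fixes the timing: "The TPE treatment will be initiated within 6 h after randomization". It adds: "Duration of TPE treatment is approximately 120–180 min". The control arm receives guideline-based standard care, and no separate starting event after randomization is described.

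The primary endpoint is death by day 28, but follow-up runs well beyond it. Under Trial design: "Study participants will be followed up at 90 days and 1 year following study inclusion".

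**The concern.** Receipt of the randomized intervention means different things in the two arms. To qualify in the TPE arm, a patient must live until the procedure, which may begin as late as 6 h after randomization. To qualify in the SOC arm, a patient need only be under standard care, which is already running at randomization. The set therefore conditions on early survival in one arm only, and the endpoint is mortality.

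The key secondary endpoints are exposed in the same direction. The plan scores SOFA as 24 for days after death up to day 7, and counts days after death up to day 28 as days with organ failure. Removing a very early death from the TPE arm thus removes a patient with close to the worst value on both.

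The compliance condition is a second selection after randomization. The follow-up period is not defined in that sentence. If it runs to the 90-day or 1-year visit, a departure from protocol after day 28 could remove a patient whose primary outcome is already recorded. That sits oddly with the consent section, which arranges for day-28 vital status to be obtained from all patients even after withdrawal of consent.

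At stake is how the PP result is read. If it shows a somewhat larger benefit than ITT, part of the difference may come from how the set is built.

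**Working it through.** **The plan's own figure.** The article gives no number for the PP set, so the planning assumptions supply the scale. For 60% vs 42%, two-sided 5% and 80% power:

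- Uncorrected: n = [1.960·√(2·0.51·0.49) + 0.842·√(0.60·0.40 + 0.42·0.58)]² / 0.18² = 119.9, i.e. 120 per group.
- Continuity-corrected: (119.9/4)·[1 + √(1 + 4/(119.9·0.18))]² = 130.8, i.e. 131 per group, as stated.

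The planned total of 274 gives 137 per arm, used below.

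**Inputs.** Control mortality is p = 60% (Sample size). The window to the start of TPE is 6 h and the session lasts 2 to 3 h (treatment-arm section). If receipt means completion, the exposed period is up to about 9 h.

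The share e of TPE-arm patients who die before TPE is **not in the document** and is assumed. As a low anchor, a constant hazard over 28 days (672 h) gives:

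- by 6 h: 1 − 0.40^(6/672) = 0.8% at 60% mortality, and 1 − 0.58^(6/672) = 0.5% at 42%;
- by 9 h: 1.2% and 0.7%.

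A hazard concentrated in the first hours would give more. The range shown is 0.5% to 10%.

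**No true effect, 60% mortality in both arms.** The TPE arm loses a share e, all deaths, and the SOC arm loses none:

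PP mortality, TPE arm = (0.60 − e)/(1 − e); PP odds ratio = 1 − e/0.60.

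| e (assumed) | Patients of 137 | PP mortality, TPE arm | Spurious benefit (points) | PP odds ratio |
|---|---|---|---|---|
| 0.5% | 0.7 | 59.8% | 0.2 | 0.99 |
| 1% | 1.4 | 59.6% | 0.4 | 0.98 |
| 3% | 4.1 | 58.8% | 1.2 | 0.95 |
| 5% | 6.9 | 57.9% | 2.1 | 0.92 |
| 10% | 13.7 | 55.6% | 4.4 | 0.83 |

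**Chance of a falsely significant benefit in the PP set.** This uses an unadjusted two-proportion test with 137 and 137(1 − e) patients: Φ[(d − 1.96·SE₀)/SE₁], where d is the spurious benefit and SE₀ and SE₁ are the pooled and unpooled standard errors. For e = 5%, d = 0.0211 and both standard errors are 0.0602, so Φ[(0.0211 − 0.1180)/0.0602] = 5.4%. For e = 1%, 3% and 10% the result is 2.9%, 4.0% and 10.8%, against a nominal 2.5%. The planned model is adjusted, so these values are approximate.

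**At the planned effect (60% vs 42%).** The PP difference is 0.60 − (0.42 − e)/(1 − e). For e = 1%, 5% and 10% this is 18.6, 21.1 and 24.4 points, against a true 18.

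**Opposing exclusions.** Suppose a share r of the TPE arm also leaves the set because patients improve before TPE and then survive. PP mortality becomes (0.60 − e)/(1 − e − r), which returns to 0.60 when r = e·0.40/0.60. For e = 3%, r = 2% cancels the bias: 0.57/0.95 = 0.60. A larger r would reverse it.

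**Under a common rule.** If early deaths stay in both arms, mortality is 60% vs 60%. If the same share is removed from both arms, it is (0.60 − e)/(1 − e) in each. Either way the odds ratio is 1.00.

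**The case against.** The strongest reply is that nothing decisive rests on the PP set. The superiority criterion and the ordered key secondary tests are primary efficacy analyses and use all randomized patients; the trimmed-means sensitivity analysis for SOFA does so too. The article nowhere says that PP must agree with ITT or is needed to confirm it. All of this stands. A reader might infer that the trial's primary conclusion is biased; the documents do not support that.

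Second, the retention of SOC patients who die early is inferred. The article does not state it, nor how death counts under compliance, and a fuller protocol or SAP may settle both. That stands in part. But the alternative of treating every death as non-compliance would leave no deaths in the PP set, so a mortality analysis would be empty. The reading used here is the only workable one, and the objection is to the rule as stated rather than to missing detail.

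Third, a reader might infer that the PP result as a whole must favour TPE, or that the distortion runs to several points. Neither follows. The direction is certain only for the early-death component, and exclusions for early recovery would pull the other way. The size depends on a share that the document does not give; at a constant hazard it is about one patient.

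Fourth, keeping patients who never received TPE in a per-protocol set may look contradictory. It is coherent: someone who dies inside a window that the protocol allows has not yet departed from the protocol.

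**Conclusion.** The concern holds for the PP set as defined. Requiring receipt of the intervention, with up to 6 h allowed before TPE, conditions on early survival in the TPE arm alone, and nothing in the article offsets this. The component favours TPE for every early-death share above zero: about 0.2 to 0.4 points at 0.5% to 1%, and 1.2 to 4.4 points at 3% to 10%, against a planned 18. These sizes rest on 60% mortality, no true effect, an assumed early-death share, and the natural reading that early SOC deaths are kept.

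The compliance clause is a separate and smaller point. Read literally, it can discard known day-28 outcomes because of later events. No direction or size can be given for it.

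The ITT conclusions are untouched. This is a flaw in a supplementary analysis, worth correcting because the correction is easy.

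**What to change.** Rewrite the PP definition in Analyses populations so that it:

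1. requires eligibility and the allocated treatment started within the window already stated in the protocol;
2. counts patients who die before that window closes as protocol-compliant in their randomized arm, with the same rule in both arms;
3. limits the compliance requirement to the intervention period or, at most, to the time point of the endpoint analysed.

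The cost is about two sentences, with no change to sample size, conduct or the primary analysis. The downside is that the PP set will contain a few TPE-arm patients who never received TPE.

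A landmark analysis that starts both arms at the end of the window may be added as a sensitivity analysis. It should be labelled as conditional on surviving the window. It would miss early harm, because it also removes patients who were treated promptly and died before the landmark, so it should not be the main PP rule.
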